#### Quality of life

Quality of life is assessed using a questionnaire from Patient-Reported Outcomes Measurement Information System (PROMIS; http://www.healthmeasures.net/index.php), which requires participants to evaluate their overall health through 10 self-reported global health items representing physical health, pain, fatigue, mental health and social health. Global Physical Health (GPH) and Global Mental Health (GMH) scales will be computed accordingly, and higher scores reflect better life quality. This scoring system has demonstrated remarkable internal consistency and reliability [40].

### Sample size calculation

As no two-arm, randomized, multi-centered, sham-controlled trial has been performed on this topic, no existing data regarding the sample size are available. However, based on our preliminary clinical data collected and a similar study [41], we assume that the mean and SD of ARLVR in the real-acupuncture group and sham-acupuncture group are (0.32, 0.25) and (0.22, 0.2), respectively, and after calculation using G-Power (V.3.1), the effect size (ES) is 0.4417261. Next we input the parameters above, set the alpha risk (α, type 1 error risk) and beta risk (β, type II error risk) at 0.05 and 0.2 respectively, and choose “t test from two independent groups” and “A Priori: Compute required sample size given α, power and effect size”, then after calculating, the required sample size is 164 (Additional file 2). Assuming the loss to follow-up rate is 20%, then 197 is the total minimum sample size required in this trial. However, to increase the power and make full preparation, we decided to recruit 200 participants, 100 for each arm in this trial.

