### Statistical and data analysis

Upon the receipt of the final data, the Kolmogorov-Smirnov test (K-S test) will be performed, followed by a test for homogeneity of variance to see whether the variances are equal between groups. If the data distribution fits a normal distribution with equal variance, the independent t test will be employed; otherwise, nonparametric test will be chosen to determine whether there is significant difference between the real acupuncture group and the sham acupuncture group. Moreover, one-way ANOVA will be performed to see whether there is significant difference between three centers. Analysis of covariance adjusted for clinical center and baseline will be applied on the condition that significant difference exists between three centers. In addition, regression analysis will be performed to analyze the effects of co-variances (risk factors) such as BMI, axillary lymph node dissection, postoperative radiotherapy, infection, and history of lymphangitis on the overall outcome of this treatment. A type I level error < 0.05 will be interpreted as statistically significant and 95% CI, mean, and SD will be calculated. Data analysis in this trial will consist of an intent-to-treat (ITT) analysis, a per-protocol (PP) analysis and an interim analysis. The ITT analysis will collect data from all the participants in this trial, and for those loss to follow-up, the last observation carried forward method will be implemented. As for the PP analysis, data collection will be rigorous, and only those participants who strictly comply with the protocol are eligible. The interim analysis in this trial performed by DSMB, will use the interim data collected during the trial to actively monitor the operating status of the trial and help find problems timely. All statistical analyses will be conducted using the SPSS software (version 12).

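### The 20% loss allowance is computed as 164 × 1.2 = 197 instead of 164 / 0.8 = 205, so the planned 200 is slightly below the true minimum, not above it

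*Protocol article*

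**What the plan says.** The section Sample size calculation of the Protocol article assumes that the means and SDs of the primary outcome (ARLVR) in the "real-acupuncture group and sham-acupuncture group are (0.32, 0.25) and (0.22, 0.2), respectively". From these it reports that "the effect size (ES) is 0.4417261", sets the type I and type II error risks "at 0.05 and 0.2 respectively", and concludes that "the required sample size is 164". It then adds the loss allowance: "Assuming the loss to follow-up rate is 20%, then 197 is the total minimum sample size required in this trial". Finally it sets the recruitment target above that figure: "to increase the power and make full preparation, we decided to recruit 200 participants", 100 per arm.

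The section Statistical and data analysis says how losses are treated. The intention-to-treat analysis takes in every participant, with last observation carried forward (LOCF) for those lost. A per-protocol analysis is restricted to those who comply strictly.

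**The concern.** A loss rate is a fraction of those enrolled. If 20% of them are lost, 80% remain, so the enrolled number must be the required evaluable number divided by 0.80. The figure 197 comes instead from adding 20% of the evaluable number to itself, which leaves too few once the loss occurs.

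The loss rate, the 164 and the 197 therefore do not agree with each other. The target of 200 inherits the problem. It is offered as something beyond the minimum, chosen for extra power and preparedness, but under the plan's own loss rate it does not reach the minimum. A reader would credit the trial with a reserve that it does not have.

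**Working it through.** **Inputs** (Protocol article, Sample size calculation): means 0.32 and 0.22; SDs 0.25 and 0.20; alpha 0.05; beta 0.2; loss 20%; 200 recruits, 1:1. Sidedness is not stated there, and the section Statistical and data analysis says only "A type I level error < 0.05 will be interpreted as statistically significant". I assume a two-sided test because that is what reproduces 164; a one-sided test would need 65 per arm, 130 in total.

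**Step 1: reproduce the effect size.**
d = (0.32 − 0.22) / √[(0.25² + 0.20²) / 2] = 0.10 / √0.05125 = 0.4417261. This matches the protocol.

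**Step 2: reproduce the 164.** Two-sided, two-sample t test with noncentral t power at d = 0.4417261:

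| Per arm | Total | Power |
|---|---|---|
| 79 | 158 | 78.8% |
| 80 | 160 | 79.3% |
| 81 | 162 | 79.8% |
| 82 | 164 | 80.3% |

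With equal arms, 82 per arm is the first size to reach 80%. The 164 is correct.

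**Step 3: reproduce the 197.**
164 × 1.2 = 196.8, rounded up to 197. Dividing by the retained fraction does not give 197: 164 / (1 − 0.20) = 164 / 0.80 = 205. With equal arms, 82 / 0.80 = 102.5, so 103 per arm and 206 in total.

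**Step 4: what loss 197 covers.**
1 − 164/197 = 0.168. It protects 164 evaluable participants against a loss of about 16.8%, not 20%.

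**Step 5: what remains at 20% loss, if those lost are not evaluable.**
- 197 × 0.80 = 157.6, about 158: power about 78.8%.
- 200 × 0.80 = 160, or 80 per arm: power 79.3%.
- Shortfall with 200: 164 − 160 = 4 participants, and 80% − 79.3% = 0.7 power points.

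**Step 6: the loss that 200 can bear.**
1 − 164/200 = 0.18. All 164 are kept only if loss is at most 18%.

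**Step 7: the intention-to-treat analysis with LOCF, as a range.** All 200 are analysed.
- If carried-forward values showed the full effect, power at 100 per arm would be 87.5%.
- As an illustrative assumption, suppose 20% in each arm are carried forward at zero change. The means become 0.8 × 0.32 = 0.256 and 0.8 × 0.22 = 0.176. The variances become 0.8 × (0.25² + 0.32²) − 0.256² = 0.0664 and 0.8 × (0.20² + 0.22²) − 0.176² = 0.0397. Then d = 0.080 / √[(0.0664 + 0.0397) / 2] = 0.347, and power is about 69%.

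The documents do not say where in this range the trial would fall.

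**The case against.** The strongest reply is that nobody is dropped. Arm volumes are measured after each session (Data collection), those who withdraw are evaluated at once where possible (Loss to follow-up and data management), and the intention-to-treat analysis carries the last value forward. On that view the sample is 200, not 160. This stands to the extent that 160 and 79.3% do not describe the intention-to-treat analysis. It does not rescue 197. The protocol adds a loss allowance, which makes sense only if lost participants are counted as not evaluable, and on that footing the divisor is 0.80. Nor does LOCF guarantee 80% power, as the range from about 69% to 87.5% shows. The per-protocol analysis loses participants in any case.

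A second reply is that the shortfall is trivial beside the uncertainty in the assumed means and SDs. That is a fair judgement of size. It does not make the stated minimum correct.

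Three stronger readings are tempting and should be resisted.
- A reader might infer that moving from 197 to 200 adds no power. It adds a little (about 78.8% to 79.3%); the error lies in the premise that 197 suffices.
- A reader might infer that 200 recruits cannot give 80% power. That follows only at a loss above 18% with lost participants left out of the analysis.
- A reader might charge a further loss of power here because the plan moves to a nonparametric test when variances differ. That is a separate matter: it arises at any sample size and is not caused by the 1.2 factor. Nor is the switch the likelier outcome under the planned SDs: simulating normal data with 80 per arm, Levene's test rejected equal variances in about 44% of trials.

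**Conclusion.** The arithmetic error stands. The stated minimum of 197 should be 205, or 206 with equal arms, and the target of 200 lies just below the minimum. At the stated loss rate the cost is four evaluable participants and about 0.7 power points, which does not endanger the design. What needs correcting is the wrong minimum and the reserve it implies.

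This rests on a two-sided t test, the protocol's assumed means and SDs, losses spread equally over the arms, and the protocol's own premise that those lost are not evaluable.

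**What to change.** In Sample size calculation, replace 197 with 164 / (1 − 0.20) = 205, or 206 for equal arms.

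Then choose one of two courses:
- Keep 200. State that it yields 160 evaluable participants and about 79% power at 20% loss, or 80% power only if loss is at most 18%. Remove the implication that 200 is a reserve above the required minimum.
- Raise the target to 206 (103 per arm), six more participants, with the centre quotas and randomization sequence adjusted to match.

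In either case, add a sentence saying that the loss allowance treats lost participants as not evaluable, and that the power of the LOCF intention-to-treat analysis depends on how much the carried-forward values dilute the effect.

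The first course costs only wording and a slightly less favourable power statement. No analysis changes under either.

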### Loss to follow-up and data management

In practice, however, participants might withdraw from the treatment program at any time. In that case, a call from the acupuncturist in charge will be given to the participant, and appropriate advice and assistance will be provided. If a participant insists on withdrawing from this trial, an instant evaluation of lymphedema status will be made, if it is possible. Complete case reports and case reports on loss-to-follow-up of the participants will be reported to the coordinators in charge every month. First-hand data will be recorded by the nurse and the acupuncturist. The coordinator in each center will collect and preserve the data every two weeks. When the trial is done, the aggregated data will be extracted by two independent researchers to guarantee the accuracy, and finally submitted to the principal investigator for analysis. During the whole process, the privacy of research participants will be fully protected.

### Statistical and data analysis

Upon the receipt of the final data, the Kolmogorov-Smirnov test (K-S test) will be performed, followed by a test for homogeneity of variance to see whether the variances are equal between groups. If the data distribution fits a normal distribution with equal variance, the independent t test will be employed; otherwise, nonparametric test will be chosen to determine whether there is significant difference between the real acupuncture group and the sham acupuncture group. Moreover, one-way ANOVA will be performed to see whether there is significant difference between three centers. Analysis of covariance adjusted for clinical center and baseline will be applied on the condition that significant difference exists between three centers. In addition, regression analysis will be performed to analyze the effects of co-variances (risk factors) such as BMI, axillary lymph node dissection, postoperative radiotherapy, infection, and history of lymphangitis on the overall outcome of this treatment. A type I level error < 0.05 will be interpreted as statistically significant and 95% CI, mean, and SD will be calculated. Data analysis in this trial will consist of an intent-to-treat (ITT) analysis, a per-protocol (PP) analysis and an interim analysis. The ITT analysis will collect data from all the participants in this trial, and for those loss to follow-up, the last observation carried forward method will be implemented. As for the PP analysis, data collection will be rigorous, and only those participants who strictly comply with the protocol are eligible. The interim analysis in this trial performed by DSMB, will use the interim data collected during the trial to actively monitor the operating status of the trial and help find problems timely. All statistical analyses will be conducted using the SPSS software (version 12).

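### Pretests on the outcome data choose the primary test, and under the plan's own unequal SDs they drop the t test that the trial was sized on in about half of trials

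*Protocol article*

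**What the plan says.** In the protocol article, Statistical and data analysis, two checks come first once the final data are in: "the Kolmogorov-Smirnov test (K-S test) will be performed, followed by a test for homogeneity of variance to see whether the variances are equal between groups". The comparison of the groups then depends on the result: "If the data distribution fits a normal distribution with equal variance, the independent t test will be employed; otherwise, nonparametric test will be chosen". The nonparametric test is not named, no unequal-variance t test is offered, and the pretests have no significance level of their own. The Abstract (Methods/Design) gives the same either-or choice. The analysis section also promises the mean, SD and 95% CI.

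Sample size calculation uses only "t test from two independent groups". Its inputs are stated thus: "we assume that the mean and SD of ARLVR in the real-acupuncture group and sham-acupuncture group are (0.32, 0.25) and (0.22, 0.2), respectively". From these, "the effect size (ES) is 0.4417261" and "the required sample size is 164".

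**The concern.** The two sections do not fit together. The trial is sized for a comparison of means in which the arms have different spreads, yet the analysis rule permits that comparison only when the spreads are found equal. The planning assumption itself therefore breaks the condition for the planned test.

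A rank test is also not the natural answer to unequal variance. When spread or shape differs between arms, it does not test equality of means. The usual answer is to keep the comparison of means and change the standard error.

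What is at stake is the primary hypothesis. Whether it concerns means or ranks would be settled by looking at the outcome data. The report could then carry a p-value from one hypothesis beside a confidence interval from the other, and the two could disagree.

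**Working it through.** **Inputs.** From Sample size calculation: means 0.32 and 0.22; SDs 0.25 and 0.20; alpha 0.05; power 80%; 164 evaluable participants (82 per arm); 20% loss; 100 recruited per arm. Three analysed sizes matter:
- 80 per arm: 100 less 20%.
- 82 per arm: the stated requirement.
- 100 per arm: everyone, since the ITT analysis carries the last observation forward.

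**Assumptions.** The pretests are run at 5%, the only significance level the section gives. The variance test is Levene's (mean- or median-centred) or the F test. The nonparametric test is Mann-Whitney. The data are exactly normal unless stated otherwise.

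**Step 1: reproduce the plan's figure.**
- Pooled SD = √[(0.25² + 0.20²)/2] = √0.05125 = 0.2264.
- Effect size = 0.10/0.2264 = 0.4417261, as stated.
- A two-sided t test at alpha 0.05 and 80% power needs 81.42 per arm, rounded up to 82, or 164 in total, as stated.

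**Step 2: the variance gate.** The variance ratio is 0.25²/0.20² = 0.0625/0.04 = 1.5625. The chance of rejecting equal variances is exact for the F test and simulated for Levene (40,000 trials):

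| Variance test | 80 per arm | 82 per arm | 100 per arm |
|---|---|---|---|
| Levene, mean-centred | 45% | 46% | 54% |
| Levene, median-centred | 43% | 45% | 52% |
| F test | 50% | 51% | 60% |

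**Step 3: both gates together.** Levene was combined with the K-S step in several versions (uncorrected per arm, Lilliefors-corrected per arm, Lilliefors-corrected on pooled data). The chance that the t test is abandoned is 43–50% at 80 per arm, 45–51% at 82 and 52–58% at 100. Real non-normality would raise it.

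**Step 4: consequence under the plan's assumptions.** The two-stage rule here is uncorrected K-S plus mean-centred Levene.

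| | 82 per arm | 100 per arm |
|---|---|---|
| Power, pooled t | 80.4% | 87.3% |
| Power, Welch t | 80.4% | 87.3% |
| Power, Mann-Whitney | 78.7% | 85.5% |
| Power, two-stage rule | 79.5% | 85.9% |
| Type I error, two-stage rule | 4.9% | 5.1% |

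The two-stage rule loses 80.4 − 79.5 = 0.9 points of power at 82 per arm and 87.3 − 85.9 = 1.4 points at 100. Welch and Mann-Whitney reach different verdicts in about 6% of trials at 80–82 per arm and about 4% at 100.

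**Step 5: stress case.** Take equal means of 0.22, SDs of 0.25 and 0.20, and unshifted gamma data. The rank test then rejects in about 15–18% of trials and Welch in about 5%. With a milder skew (shifted gamma), the rank test rejects in about 7%.

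**The case against.** Four points can be made in defence of the plan.

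1. **The rule does little harm on the plan's own figures.** This stands. Under normality the two tests behave alike, and choosing between them costs about 1 point of power. A reader might infer from the near-even switch that the trial's error rates are in danger; the calculations do not show that.

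2. **The 15–18% rejection rate comes from an unsuitable distribution.** This also stands. The gamma shapes are (0.22/0.25)² = 0.77 and (0.22/0.20)² = 1.21, which exclude negative values. ARLVR can be negative: worsening of lymphedema is listed among the possible adverse events, and the plan's own normal model puts Φ(−0.32/0.25) = 10% of the real arm and Φ(−0.22/0.20) = 14% of the sham arm below zero. Nothing in the document supports the gamma shape, so the figure shows what a rank test can do and does not forecast this trial.

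3. **Ranks may be a safeguard for this outcome.** This stands in part. Under Primary outcome, the words define ARLVR relative to the baseline excess volume, but the printed formula divides by the change in the affected arm (V_AB − V_AL), which can be close to zero. As printed, the ratio could have extreme tails and its mean would be unstable. It would therefore be too strong to say that the pretests could never protect; that holds only with the verbal definition.

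4. **The rule is conventional, written down in advance, and names no rank test.** Writing a rule down does not fix the hypothesis when the rule lets the outcome data choose it. That the alternative is a rank test is indeed an inference; leaving it unnamed makes the primary analysis looser still.

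**Conclusion.** The point holds as a fault of specification, worth correcting but of modest numerical size. The test on which the trial was sized is conditional on an equality that the sizing itself denies. On the plan's own SDs it would be set aside in about 43–51% of trials at 80–82 per arm and 52–58% at 100 per arm (60% at 100 if the F test alone is the gate). The gate gains no power over Welch, and in about 4–6% of trials the choice between Welch and ranks changes the conclusion.

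The document does not support a claim of materially inflated type I error or a serious loss of power. Under the stated normal assumptions, error stays near 5% and the loss is about 1 point.

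The conclusion assumes pretests at 5%, a Levene or F test, a rank test as the alternative, and ARLVR computed with the baseline excess volume as denominator.

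**What to change.** First reconcile the printed ARLVR formula with its verbal definition, since a comparison of means is dependable only if the denominator stays away from zero.

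Then change the protocol text in Statistical and data analysis and in the Abstract:
- Remove the K-S and variance tests as conditions for choosing the primary test. They may remain as descriptive checks.
- Name one primary analysis: the difference in mean ARLVR with its 95% CI, by a Welch t test or by an adjusted model with heteroscedasticity-robust standard errors.
- Name the rank test and report it as a sensitivity analysis.

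Whether the covariance analysis should depend on a centre difference is a separate question, and this change does not need it settled.

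The cost is wording in the protocol, with any analysis plan brought into line. The sample size stands as far as this point goes: Welch power is 80.4% at 82 per arm and 87.3% at 100, the same as for the pooled t test.

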### Randomization and allocation

Eligible participants in each center are randomized into the real acupuncture group and the sham-acupuncture group at a ratio of 1:1 according to the randomization sequence, which is a series of randomization numbers representing each patient’s unique number, and pre-generated by the chief designer using RAND function in Microsoft Excel program according to the quota of each center (Additional file 1).

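### Adjustment for centre and baseline hangs on a significance test between centres, which leaves the primary analysis ambiguous and may cost precision

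*Protocol article*

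**What the plan says.** The Statistical and data analysis section sets out a sequence of tests. It begins: "Upon the receipt of the final data, the Kolmogorov-Smirnov test (K-S test) will be performed". A test of equal variances follows, and then the choice of method: "If the data distribution fits a normal distribution with equal variance, the independent t test will be employed", with a nonparametric test otherwise. Next, "one-way ANOVA will be performed to see whether there is significant difference between three centers". The variable in that ANOVA is not named. Finally, "Analysis of covariance adjusted for clinical center and baseline will be applied on the condition that significant difference exists between three centers". The section does not say whether the ANCOVA then takes the place of the two-group test or stands beside it, and it does not define baseline. A separate regression on risk factors names neither centre nor baseline volume.

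The Randomization and allocation section states: "Eligible participants in each center are randomized into the real acupuncture group and the sham-acupuncture group at a ratio of 1:1", from a sequence generated according to each centre's quota. The Data collection section has both arms of every participant measured by perometer before the first session.

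**The concern.** Centre is built into the allocation and is known before any outcome is seen. The usual principle is that a factor used in randomisation stays in the model whatever a test shows. A non-significant comparison of three unequal centres is not evidence that centre can be ignored.

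The gate is also the wrong one for baseline. Whether centres differ has no bearing on whether baseline excess volume predicts the outcome, yet baseline adjustment is allowed only when they do.

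Two things are at stake. One is precision, if centre or baseline is prognostic. The other is clarity: when the gate opens, the trial may hold two p-values for one primary outcome, and the plan does not say which is primary.

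**Working it through.** **1. The plan's own figure.** Inputs from Sample size calculation: the means and SDs of ARLVR "are (0.32, 0.25) and (0.22, 0.2), respectively"; and "set the alpha risk (α, type 1 error risk) and beta risk (β, type II error risk) at 0.05 and 0.2 respectively".

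- Pooled SD = √((0.25² + 0.20²)/2) = 0.2264.
- d = (0.32 − 0.22)/0.2264 = 0.4417, which matches the stated effect size.
- Exact two-sided t test at 0.05: 82 per arm, 164 in total, power 0.803. The stated 164 reproduces. It rests on an unadjusted comparison.
- The plan recruits 200 and assumes 20% loss: 200 × 0.8 = 160 evaluable, or 80 per arm.

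**2. How often the gate would open.** Quotas follow yearly patients of about 400, 200 and 120 (Study setting/design). This gives 111/56/33 of 200, or about 89/44/27 of 160. Assume true centre offsets in ARLVR of +δ, 0 and −δ, in that order of centre size. The noncentrality of the F test is λ = N × (between-centre variance)/SD². The between-centre variance is 0.000514 at δ = 0.03 and 0.001427 at δ = 0.05.

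| δ | N | λ (SD 0.2264) | Gate opens |
|---|---|---|---|
| 0.03 | 200 | 2.01 | about 22% |
| 0.03 | 160 | 1.60 | about 18% |
| 0.05 | 200 | 5.57 | 52–54% |
| 0.05 | 160 | 4.46 | 43–45% |

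The ranges depend on whether the treatment difference is counted in the SD. The offsets are assumptions; the documents give none.

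**3. What missing those centre differences costs.** Share of variance due to centre = between-centre variance/(between-centre variance + SD²):

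- δ = 0.03: 0.000514/(0.000514 + 0.05125) = 1.0%.
- δ = 0.05: 0.001427/(0.001427 + 0.05125) = 2.7%.

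With 80 per arm, removing 1% of variance moves power from 79.3% to 79.7%. Removing 3% (2.7% rounded up) moves it to 80.5%. The gain is about 0.4 to 1.2 points.

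**4. What always adjusting for centre and baseline could gain.** Power is computed with d/√(1 − R²), 80 per arm. R² is an assumption and includes the no-gain case.

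| R² | Power |
|---|---|
| 0 | 79.3% |
| 0.05 | 81.3% |
| 0.10 | 83.3% |
| 0.20 | 87.4% |

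**5. The gated rule against ANCOVA always, by simulation.** There were 10,000 runs per scenario with 166 patients (164 rounded to even numbers within centre), 1:1 within centre. R² here is the share explained by baseline, and the between-centre SD is in units of outcome SD.

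| Between-centre SD | Baseline R² | Gate opens | Power, gated | Power, always ANCOVA |
|---|---|---|---|---|
| 0 | 0 | 4% | 0.805 | 0.803 |
| 0 | 0.10 | 5% | 0.805 | 0.840 |
| 0 | 0.25 | 4% | 0.810 | 0.900 |
| 0.15 | 0.10 | 37% | 0.820 | 0.842 |
| 0.15 | 0.25 | 37% | 0.837 | 0.903 |
| 0.30 | 0.10 | 93% | 0.838 | 0.840 |
| 0.30 | 0.25 | 93% | 0.893 | 0.900 |

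The loss is largest where baseline is prognostic and centres do not differ, because the gate then withholds the useful adjustment. With no treatment effect, the gated rule rejected in 0.045 to 0.055 of runs across all scenarios, against a nominal 0.05.

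**The case against.** **The benefit is not shown in the documents.** This stands. No correlation between baseline volume and ARLVR is given. The outcome is described as a proportion of baseline excess volume, and the Discussion presents it as excluding base effects, so an R² near 0 is plausible and nothing would then be gained. But the plan itself names baseline as a covariate, and a ratio can still depend on its starting value.

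**The centre gate alone costs little.** This also stands. Where it often misses a real centre difference, the loss is about one power point or less. The low trigger rates must not be read as the cause of the larger gains in step 4, which would come almost wholly from baseline.

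**The full 200 may be analysed.** The intent-to-treat analysis carries the last observation forward. If all 200 are counted at the assumed effect, unadjusted power is 87.5%, and R² of 0.05 to 0.20 gives 89.0% to 93.5%. The gain is smaller but of the same kind.

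**A stronger reading is tempting:** that the model is picked after seeing the treatment result, so false positives rise. The documents do not support it. The rule is written in advance, it tests centre and not treatment, and its simulated type I error is nominal. Simulated error reaches about 0.05 to 0.09 only if the better of the two p-values could be reported, and the plan does not permit that choice. Nor is it certain that the gate uses outcome data. That is the natural reading, since testing follows receipt of the final data, but the variable is not named.

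**Conclusion.** The point holds as one of efficiency and clarity. The plan states a conditional rule that has no sound basis for a randomisation factor or for a baseline measured in everyone, and it leaves open whether the ANCOVA replaces or supplements the two-group test. The validity of the comparison is not threatened.

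The size depends on a covariate R² that the documents do not give. With 160 evaluable patients the gain from always adjusting runs from nothing at R² = 0 to 8.1 points (87.4 − 79.3) at R² = 0.20. Confidence is high that the text says this and that the rule should change; it is low on how much power is lost. The change is still worth making, because it costs nothing and because 160 evaluable patients would be 4 short of the plan's own 164.

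**What to change.** - Name one primary analysis: an ANCOVA of ARLVR on arm, centre (three levels) and a defined baseline covariate, applied unconditionally, with the adjusted mean difference and 95% CI.
- Define the covariate, for example baseline excess volume V_AB − V_UB. First reconcile the Primary outcome section: its formula divides by V_AB − V_AL, while its text describes the denominator as the excess volume before therapy. The role of the covariate depends on which is meant.
- Drop the between-centre ANOVA as a gate. Centre differences can still be described.
- State that the primary model stands whatever the Kolmogorov-Smirnov and variance tests show, for example with robust standard errors.
- Report the unadjusted or nonparametric comparison as supportive.

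The cost is analysis wording, settled before unblinding. No new data, procedures or patients are needed, and the sample size calculation can stay on its unadjusted basis, since any gain from adjustment adds to it.
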